## Abstract

**Background:**

Service disengagement is a pervasive challenge the mental health care system faces. Mental health services are of little value should persons with mental illnesses continue to opt out of receiving them. Consumers attribute disengagement from care to an absence of choice in their treatment. In response, the mental health system is adopting a person-centered model, based upon recovery principles, to engage consumers more actively in their care. Person-centered care planning is a promising practice involving collaboration to develop and implement an actionable plan to assist the person in achieving personal recovery goals.

**Methods/design:**

This study design combines a parallel-group randomized controlled trial of community mental health organizations with qualitative methods to assess the effectiveness of person-centered care planning. Participants at 14 sites in Delaware and Connecticut will be randomized to treatment as usual or the person-centered care planning intervention. Participants will be in leadership (n = 70) or supervisory or direct care (n = 210) roles. The person-centered care planning intervention involves intensive staff training and 12 months of ongoing technical assistance. Quantitative survey data will be collected at baseline, 6 months and 12 months measuringperson-centered care planning competency and organizational factors. Consumer outcomes (engagement, medication adherence, functioning and consumer satisfaction) will be assessed by Medicaid and state-level data. Qualitative data focused on process factors will include staff and consumer interviews and focus groups. In this intent-to-treat analysis, we will use mixed-effects multivariate regression models to evaluate the differential impact of the person-centered care planning intervention on each consumer and implementation outcome as well as the extent to which clinician assessments of organizational factors are associated with the implementation outcome. Mixed methods will triangulate and strengthen the interpretation of outcomes.

**Discussion:**

The aim of this study is to generate valuable guidance for state systems engaged in scale-up and transformation efforts. Targeted staff selection for training to support sustainability will serve to provide further insight into important intervention implementation strategies. Person-centered care planning has the potential to enhance the impact of all evidence-based and recovery-oriented practices and bring practice into line with the emerging national guidelines in health care reform.

**Trial registration:**

This trial was registered with ClinicalTrials.gov (Identifier: NCT02299492) on 21 November 2014 as New York University Protocol Record PCCP-13-9762, Person-Centered Care Planning and Service Engagement.

## Background

Service disengagement is one of the most pervasive and challenging problems currently facing the mental health care system [1,2]. Epidemiological studies have shown that 33% to 55% of people who meet criteria for an axis I diagnosis (according to the *Diagnostic and Statistical Manual of Mental Disorders, Fourth Edition* [3]) have received no mental health care in the past year [4]. Of those who do seek care or are hospitalized, an estimated 24% do not attend treatment sessions as scheduled, 20% drop out of treatment before it is completed, and 18% to 67% do not attend outpatient treatment after hospitalization [1,5]. During the Clinical Antipsychotic Trials of Intervention Effectiveness study, 64% to 82% of patients dropped out of treatment within the first year [6]. No matter how effective mental health services are now or become in the future, they are of little value should persons with mental illnesses continue to choose not to receive them.

Although there are many reasons why people disengage from care [7], people’s experience of the treatment process is one significant factor that can be addressed by practice innovation. Consumers have attributed their disengagement from care to having poor alliances with care providers, including experiences of not being listened to and not being offered the opportunity to make decisions and collaborate in their own treatment [5,8]. In response, the mental health system is moving toward a more person-centered model, based upon recovery principles, to engage consumers more actively in their own care [9]. States have embraced this model in theory, and they are now looking for guidance on how best to implement this model in practice, including how to maximize service quality and consumer outcomes, given the limited resources available to them for workforce development [10]. The proposed study tackles this pressing issue by testing the effectiveness of person-centered care planning (PCCP), a manualized, provider-based intervention that maximizes consumer choice for adults receiving mental health services [11]. By targeting the service-planning process that is shared by all evidence-based practices (EBPs) and mental health services, PCCP embeds a value-added component throughout the agency.

### Person-centered care planning

PCCP makes real a service approach that has been championed by the Institute of Medicine and the New Freedom Commission on Mental Health [12,13]. By shifting from an illness and/or deficit focus to a strengths-based, person-centered one, this intervention fundamentally changes a practice culture that has resulted in many people walking away from the care they need. Instead, PCCP offers an opportunity for people to enter into a genuine partnership with the care system to improve the overall quality and effectiveness of care. PCCP emerged from the federal agenda to transform mental health care to a recovery orientation and is now being adopted at the state level [14]. Models of PCCP were initially developed and found effective for use with persons with developmental disabilities in the 1980s [15,16]. With two randomized trials and evaluations at the state level demonstrating positive results, PCCP has been identified as a promising practice [17,18]. PCCP involves a collaborative process between the service user and all of those people in the person’s life whom he or she identifies as supportive of his or her recovery, including clinical practitioners, other mental health staff involved in the person’s care, and any natural supporters (for example, friends, family members, representatives from faith communities). The aim of the planning process is to develop and implement an actionable plan to assist the person in achieving his or her unique personal goals along the journey of recovery. This plan is also intended to address the specific mental health and/or substance use barriers interfering with the person’s goal achievement, and in this way it is able to meet the rigorous documentation elements required by accrediting and funding bodies (that is, the Joint Commission and Centers for Medicare and Medicaid Services).

Person-centered care plans are (1) oriented toward promoting recovery rather than only minimizing illness and symptoms; (2) based on the person’s own unique life goals and aspirations; (3) focus and build on the person’s capacities, strengths and interests; (4) articulate the person’s own role and the role of both paid practitioners and natural supports in assisting the person to achieve his or her own goals; (5) emphasize the use of natural community settings rather than segregated program settings; and (6) anticipate and allow for uncertainty, setbacks and disagreements as inevitable steps on the path to greater self-determination [10]. These principles make PCCP truly transformative and ultimately sustainable, but they also create challenges when implemented in real-world settings. As with other recovery-oriented practices, PCCP demands a profound shift in values and culture that has implications for providers, organizations and systems [19]. Therefore, sustainable changes in provider behavior may be most likely when training is accompanied by corresponding changes in beliefs, attitudes, and organizational culture, policies and structures.

Prior research has indicated that PCCP is a promising practice across a variety of settings. In one study, researchers randomized five community mental health clinics (CMHCs) to the PCCP condition and five CMHCs to treatment as usual, with providers in the experimental settings receiving training and ongoing coaching in PCCP [18]. The experimental condition had fewer “no shows”, demonstrating higher levels of consumer engagement, and clinicians reported higher rates of medication adherence as compared with the control sites. In a second randomized controlled trial, PCCP was combined with illness management and recovery and a peer-run community integration program for low-income adults of Hispanic and/or African origin with psychotic disorders [17]. The intervention was found to be effective in increasing participants’ active involvement in the care-planning process and in increasing inclusion in the planning process for housing, employment and education. The intervention also increased participants’ sense of control and efficacy in their self-care and overall lives, reduced psychotic symptoms and increased family and social support. Although both of these studies indicated that PCCP was effective, PCCP was combined with other interventions, making its specific impact hard to assess. In addition, researchers have documented concerns specific to implementing recovery-oriented practices, including PCCP. These include beliefs that recovery oriented practice is not unique or novel, that it is too burdensome for overextended clinicians, that it is not desired by people with severe mental illnesses, that it is not evidence-based or reimbursable, that it devalues provider expertise, and that it is too risky because it increases provider exposure to incidents and liability [20,21]. Such concerns pose formidable barriers to implementation if not addressed. To address and further evaluate these concerns, data will be collected on organizational factors to assess if differences in organizational culture impact the implementation of PCCP.

### Conceptual framework and causal model

The primary aim of the study is to examine the effectiveness of PCCP while also seeking to assess the influence of organizational variables on the implementation of PCCP and its impact on consumer outcomes. The conceptual framework integrates implementation science and mental health recovery to hypothesize causal relationships between the organization, provider and service user.

#### Organizational factors

The organizational level assessment targets three organizational factors: transformational leadership, recovery orientation and organizational readiness. Positive change in these three factors is hypothesized to bring about the necessary organizational conditions for successful training of providers in PCCP and improvement in service user outcomes (see Figure 1 for causal model used in this study).

**Figure 1 Fig1:**
[figure not shown]
Causal model of person-centered care planning (PCCP).

Transformational leadership is a key upstream organizational factor in creating mental health service organizations that are open to change [22], can improve client outcomes [23] and are recovery-oriented [24]. The leadership qualities that promote transformation are those that inspire providers to adopt the values and goals of their leaders [25]. As opposed to focusing on the completion of specific tasks (transactional leadership), transformational leaders motivate providers by conveying a shared sense of mission and heightening expectations for performance. Recovery orientation is the specific values–innovations fit [26] needed to successfully implement PCCP. Moving toward genuinely person-centered care involves not simply technical skills but also a paradigm shift in how providers understand and value their work with consumers. Nine principles have been identified with regard to recovery orientation, including renewing hope and commitment and redefining self and assuming control [27]. Organizational readiness, which captures both motivation and capacity for change, is now recognized as a critical precursor to successful adoption of innovation in behavioral health care settings [28]. This multifaceted construct reflects how the sum of individual attitudes and behaviors operate at a collective level within an organization [29]. First, staff must be motivated to change by a perceived need for new skills and have confidence in their own ability to adapt to, master and share new skills. Second, organizational climates conducive to change must convey a clear sense of mission and goals, promote staff cohesion and cooperation, and reflect an openness to change. Third, change must be supported by the necessary resources, which include adequate staffing, training, equipment and alignment of procedures [30].

#### Person-centered care planning competency

PCCP competency is the extent to which providers adhere to the intervention (fidelity) and demonstrate the necessary value endorsement and skills to implement PCCP. High-quality PCCP consists of four components: (1) believing people have a right to self-determination, (2) interacting with persons with respect and projecting a hopeful vision for the future, (3) producing a high-quality written service plan and (4) having high expectations for outcomes related to life goals. In accordance with the PCCP manual, the intervention targets provider attitudes and behaviors related to these four areas with training of clinical supervisors and provision of technical assistance (TA) for a 1-year period.

#### Outcomes

Study outcomes are impacted by the choice and perceived relevance of the services offered to consumers. Increasingly, service engagement and adherence are being understood as a function of choice that operates within the broader context of the myriad decisional and social processes that occur when a person enters care [7]. Therefore, whether people choose to use medication or services is determined in large part by the extent to which people feel that they have had a choice leading up to these specific adherence decisions. Self-determination also requires that choices be directly relevant to an individual’s values, preferences and life goals rather than just choosing between limited options that are not perceived to increase quality of life [31]. Service engagement that is precipitated by an increase in self-determination has been found to be associated with greater satisfaction with services [32]. PCCP seeks to maximize choice and ownership of the treatment process by engaging people in care that is relevant and responsive to their holistic needs and life goals. This increases the likelihood that they will adhere to and benefit from treatment. Making decisions, considered a fundamental “capability” needed in order to pursue a meaningful life [33], nevertheless may not be a readily accessible skill for those who have not had control over their lives for many years. PCCP also addresses what Deegan referred to as “learned helplessness” [34] by offering consumers not only choices but also the supports and skills they need in order to achieve higher functional status and regain a sense of control over their lives.

## Methods

This trial has three aims. Aim 1 and Aim 2 utilize quantitative methods and Aim 3 utilizes qualitative methods.

Aim 1 is to assess the effectiveness of PCCP. Aim 2 is to assess organizational factors in the implementation and effectiveness of PCCP.

### Participants

We randomly selected 14 research sites from among all community mental health clinics (CMHCs) in Delaware and Connecticut. These agencies serve approximately 8,000 consumers. We used the Power and Precision software package (Biostat, Englewood, NJ, USA) to calculate sample sizes needed to achieve 80% power (α = 0.05) to detect these effects in our two-level hierarchical design where clinicians and patients are nested within CMHCs. The software accounts for this nesting using the intracluster correlation coefficient (ICC), a measure of the relatedness of clustered data that compares the variance within and between clusters. The ICC in our pilot data was 0.013. To achieve the study aims, we will need 280 participants (20 per site). We will need 1,125 medical record reviews (75 per site).

The services delivered at the CMHCs include psychiatric crisis intervention, individual and group therapy, psychiatric evaluation, medication management, case management, community support programs and rehabilitation services. A total of 280 providers will be recruited for the study. Within each research site, five clinical supervisors, ten direct care staff and five leadership staff will be recruited to participate in the study. The supervisors are clinical staff who are directly responsible for supervising the direct care staff. Direct care staff are clinicians who provide frontline services to consumers without any supervisory duties. The supervisors and direct care staff work in the outpatient mental health programs listed above. They come from a variety of disciplines, including social work, psychology, psychiatric rehabilitation, counseling and peer support. The leadership staff are in administrative positions and do not directly supervise direct care staff. Their titles include executive director, medical director, administration direction, operations director, quality improvement director, clinical services directors, peer support or consumer affairs director, training and staff development director, rehabilitation services director, human resources director, and representatives from the agency’s consumer advisory council.

Each supervisor will nominate two direct care staff who report to them. They will nominate individuals based on whether they fulfill the criteria of change agents, which are that they have worked at the agency for more than 1 year, have demonstrated leadership potential, are open to change and adoption of new practices and are perceived as a resource and/or role model by other direct care staff.

Secondary data will be used to assess consumer outcomes. Consumers eligible for this study will be adults who have received services at the CMHCs continuously for 1 year prior to the study. We will use the Medicaid and state mental health data of all eligible consumers.

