### Randomization

The 14 sites (8 in Connecticut and 6 in Delaware) selected for the study will be randomized into the 2 study arms, yielding 7 sites per condition, balanced by state. A research team member will use SAS 9.3 software to generate the allocation sequence assigning sites to condition. The software will generate randomized lists blocked by state, ensuring three experimental sites and three control sites in Delaware and four experimental sites and four control sites in Connecticut. The responsible team member will be blinded to site-specific information during randomization. Blinding is not possible, given the circumstances of the intervention.

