### Measurement

The intervention will be conducted over a period of 12 months and will be staggered across experimental sites. Organizational factors and PCCP competency will be measured by surveys of the leaders, clinical supervisors and direct care staff because reliable assessment requires multiple perspectives [30]. These surveys will be administered at baseline, 6 months and 12 months. Chart reviews will also be used to measure PCCP competency. Service engagement and consumer outcomes will be measured using state mental health data and Medicaid claims data.

Online assessment measures will be administered to all study participants, regardless of treatment condition. Researchers will collaborate with each CMHC to identify the leadership staff, clinical supervisors and direct care staff. An e-mail with an embedded URL linking participants to the online consent form and survey will be sent to each provider individually. Depending on their role in the agency, staff will receive one of the three surveys for direct care staff, clinical supervisors or executive leadership. The surveys are substantively equal with variation in the measurement versions and included language. Surveys will be completed at three time points: baseline, the midpoint of the intervention period (6 months) and postintervention (12 months). Each research site in the control condition will be paired with a site in the experimental condition, and the surveys will be e-mailed to pairs 1 month prior to the experimental site’s receipt of the PCCP intervention. Chart reviews will assess 75 service plans per site before and after the intervention.

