In the analyses for aim 1, we will assess the effectiveness of PCCP on service engagement and clinical outcomes. We will use each outcome as the dependent variable and a dichotomized measure of the PCCP intervention (any intervention versus no intervention) as our independent variable. Controlling for relevant baseline characteristics and including a fixed effect for state, we will use separate mixed linear regression models to determine the impact of the intervention on each of the outcomes at each time point. The primary ITT test and estimation will be done at the 24-month time point with tests at earlier time points. We will then conduct a growth curve analysis with repeated observations representing measures at baseline, 12 months and 24 months. The analysis will include variables for time, treatment and their interaction, but it will be focused on the magnitude and statistical significance of the time × treatment interaction to quantify the relative difference in the rate of outcome change between the treatment groups. All models will include random intercepts and slopes for CMHC and state. We will repeat these analyses to compare each intervention arm to treatment as usual.

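### The stated need for 1,125 chart reviews does not follow from 14 sites at 75 each (1,050 per time point), and one analysis sentence refers to several intervention arms in a two-arm trial

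*Protocol article*

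**What the plan says.** All references are to the protocol article.

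- **Number of sites.** Methods, Participants (the quantitative section): "We randomly selected 14 research sites from among all community mental health clinics (CMHCs) in Delaware and Connecticut". Randomization gives the split by state, "The 14 sites (8 in Connecticut and 6 in Delaware) selected for the study", and says that they will be "randomized into the 2 study arms, yielding 7 sites per condition, balanced by state".
- **Chart reviews.** The sample-size text in Participants, which aims at 80% power with alpha 0.05 and cites a pilot intracluster correlation of 0.013, states: "We will need 1,125 medical record reviews (75 per site"). Measurement repeats the per-site figure and adds the timing: "Chart reviews will assess 75 service plans per site before and after the intervention".
- **Staff.** The same sample-size text asks for 280 participants at 20 per site.
- **Arms in the analysis.** For Aim 1, Quantitative Data analysis uses "a dichotomized measure of the PCCP intervention (any intervention versus no intervention) as our independent variable". It later adds: "We will repeat these analyses to compare each intervention arm to treatment as usual".

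**The concern.** A required sample size and its per-site figure are printed in the same sentence, and they do not agree for the number of sites in the trial. The chart total is presented as an output of a power calculation, and the effect size behind that calculation is not given as a number. The total is thus one of the few outputs that a reader can check, and it fails. The reader cannot tell whether the total or the per-site number is wrong, whether the total counts one time point or two, or whether the calculation was made for seven sites against seven. Chart reviews are one of the two sources for PCCP competency, which the Aim 2 analysis names as the primary implementation outcome.

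The analysis text has a mismatch of its own. Grouping any intervention together and then separating each intervention arm has a purpose only with two or more active arms. This trial has one.

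**Working it through.** **Inputs**

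- Sites: 14 (8 + 6), seven per arm (Participants; Randomization).
- Chart reviews per site: 75 (Participants; Measurement), before and after the intervention (Measurement).
- Stated chart total: 1,125 (Participants).
- Stated staff total: 280 at 20 per site (Participants).
- Power 80%, alpha 0.05, intracluster correlation 0.013 (Participants). Sidedness is not stated; I assume two-sided.

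**1. Can the stated total be reproduced?** Total = sites × reviews per site.

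| Reading | Calculation | Result | Gives 1,125? |
|---|---|---|---|
| 14 sites, one time point | 14 × 75 | 1,050 | No |
| 14 sites, both time points | 14 × 75 × 2 | 2,100 | No |
| 15 sites, one time point | 15 × 75 | 1,125 | Yes, but there are 14 sites |
| Per-site number implied by 14 sites | 1,125 / 14 | 80.4 | Not a whole number, and not 75 |
| Allowance for lost charts | 1 − 1,050 / 1,125 | 6.67% | Only at this rate, and no allowance is stated |

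The gap is 1,125 − 1,050 = 75 reviews, or 75 / 1,125 = 6.7% of the stated need.

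**2. Cross-check on staff.** 14 × 20 = 280, which reproduces the staff figure exactly (15 sites would give 300). The mismatch is confined to the chart total.

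**3. What the gap costs in precision.** For reviews clustered in sites,

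- design effect = 1 + (75 − 1) × 0.013 = 1.962;
- detectable difference in SD units = (1.96 + 0.84) × √(2 × 1.962 / n per arm), normal approximation.

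Results:

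- 1,050 reviews, 525 per arm: 2.80 × √(3.924 / 525) = 0.242 SD.
- 1,125 reviews, 562.5 per arm, same design effect: 2.80 × √(3.924 / 562.5) = 0.234 SD.

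The ratio is √(1,125 / 1,050) = 1.035, so the detectable difference is about 3.5% larger. The second line treats the extra 75 reviews as an extra site. If they came from about 80.4 reviews at each of the 14 sites, the design effect would be 1 + 79.4 × 0.013 = 2.03, and the detectable difference 2.80 × √(2 × 2.03 / 562.5) = 0.238 SD. The gain over 1,050 would then be smaller still.

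**4. The arms, side by side.** Randomization defines two arms with "yielding 7 sites per condition, balanced by state": PCCP and treatment as usual. The Aim 1 text sets up one contrast, any intervention against none, and then repeats the analyses for each intervention arm. With a single intervention arm, the repeat is the same contrast.

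**The case against.** The strongest reply is that this is a single slip in multiplication. The site count and the 75 per site are each stated consistently wherever they appear, and these are what drive power in a clustered design. The staff sample agrees with 14 sites. The charts do not size the engagement and clinical outcomes of Aim 1, which use Medicaid and state data on all eligible consumers. The Mixed methods section already concedes a possible lack of power for implementation outcomes. The sentence on separate arms blocks nothing: with one arm, it duplicates a comparison already specified. All of this stands, and it limits the weight of the point. It does not make 14 × 75 equal 1,125, and fuller documents could explain the printed figures but not make them agree.

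Two stronger readings are tempting, and the document supports neither.

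- **A leftover design.** A reader might infer that 1,125 and the plural arms survive from a plan with 15 sites or several intervention arms. The document mentions no such plan, a plain slip explains 1,125 equally well, and the staff figure fits 14 sites. It also does not follow that the study as a whole was sized for a different design.
- **A departure from intent to treat.** A reader might take any intervention versus none as actual exposure. The Quantitative Data analysis section says that all analyses are by intent to treat, compares the two arms, plots trajectories by assigned treatment and names a primary ITT test. Since whole sites are assigned, the variable can be read as the arm indicator. The wording is loose, but no conflict is shown.

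**Conclusion.** The point holds as an inconsistency to be reconciled. The chart total of 1,125 is wrong for 14 sites at 75 per site. The design as described gives 1,050 per time point and 2,100 over both, so the stated requirement is missed by 75 reviews at each time point.

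The effect on precision is small: about 0.242 SD against 0.234 SD, assuming two-sided alpha 0.05, 80% power, an intracluster correlation of 0.013 that applies to chart scores, 75 reviews per site in the design effect, and a normal approximation. This is not evidence of serious underpowering. Because no numeric effect size is given, the power calculation cannot be reproduced. The document therefore does not settle whether the total or the per-site number should change, or which number of sites the calculation used.

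The sentence on each intervention arm contradicts the two-arm design. It is redundant, not impossible to carry out.

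**What to change.** 1. In Participants, restate the chart sample as 1,050 reviews per time point (75 × 14) and 2,100 in total. If 1,125 is what the power calculation requires, reconcile it with the per-site figure instead: 14 × 80 = 1,120 falls short, so it would take 81 per site (14 × 81 = 1,134), and Measurement would have to change to match. Either way, say whether the total counts one time point or both.
2. Confirm that the power statement was computed for seven versus seven sites, or rerun it for that design.
3. In Quantitative Data analysis, delete the sentence on comparing each intervention arm with treatment as usual.
4. In the same section, word the independent variable as the randomized assignment of the site.

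The cost is a few changes of wording and at most one rerun of the power calculation. On the first option, no change in data collection is needed, and the stated size becomes slightly less favourable. Raising the per-site number would add chart reviews: six more per site at each time point, or 84 across the 14 sites.
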